### 2.6. Intervention

Enrollment will occur within 48 h from birth, typically within the first 24 h of life. During this process, patients will undergo screening for both inclusion and exclusion criteria.

Infants in the monitored group will receive an initial dose of 1000 IU of vit D (cholecalciferol/Devikap; Polpharma, Starogard Gdański, Poland), whereas infants in the controlled group will receive 250 IU for extremely low birth weight infants and 500 IU for infants weighing above 1000 g. The administration of vit D will occur just before feeding via an orogastric tube, until the infants commence bottle feeding directly by mouth. Parenteral nutrition includes an additional 160 IU/kg of vit D, and enteral nutrition comprises 150–300 IU/kg, depending on the quantity and source of enteral feeding (e.g., human milk fortifiers or milk formula). At 28 ± 2 days of age, blood samples will be obtained for 25(OH)D concentration measurement, followed by measurements every 4 weeks and/or 35 ± 1 weeks of PCA. In the monitored group, vit D doses will be adjusted accordingly based on the 25(OH)D levels, following the scheme outlined in the Polish recommendation (Table 2) [7]. Dietary intake will be calculated starting in the 2nd month of life.

Infants assigned to the standard therapy group will undergo the same blood sample collection procedure as the monitored group, but without any alterations in their dosing regimen. If we observe a potentially toxic level of >100 ng/mL, we will stop supplementation in both groups for ethical reasons.

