#### 2.9.1. Nephrocalcinosis and Nephrolithiasis

Neonatal staff will collect venous samples (0.7 mL) for the Ca-P metabolism tests, including serum and urine calcium, and creatinine level measurements at 28 ± 2 days of life and at 35 ±1 weeks of PCA. The measurements will be performed using the AU480 chemistry analyzer from Beckman Coulter. The calibration of the analyzer will be verified with suitable controls, following the product guidelines. Hypercalcemia will be defined as a serum level of ≥2.75 mmol/L. Hypercalciuria will be assessed by determining urine calcium-to-creatinine ratios, which vary, depending on the individual’s age [32]. Malone et al. reported that infants born prematurely with lower birth weights and immature kidneys face heightened susceptibility to nephrocalcinosis, the risk factor of smaller kidneys, obstructive hydronephrosis, and hypertension [33]. They observed a trend toward higher average serum 25(OH)D concentrations among preterm infants with nephocalcinosis. The incidence of nephrocalcinosis was high at 41% (23/56) in infants born at ≤32 weeks gestational age. Therefore, monitoring of both the 25(OH)D level and serum and urine calcium levels is recommended in this group of premature neonates. In infants, excess levels of urine calcium and creatinine are considered risk factors for nephrolithiasis. At 35 ± 1 weeks of PCA, infants will undergo a nephrocalcinosis assessment conducted by two independent and skilled ultrasonographers (blinded to the group and other ultrasonographers) using the HD11 XE ultrasound system (Philips Healthcare, Andover, MA, USA). Nephrocalcinosis will be identified by heightened medullary echogenicity, characterized by small white flecks at the tip of the pyramids. Photographic documentation will be captured.

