### 2.11. Data Monitoring

We opted not to establish a data monitoring committee since the intervention in the trial (i.e., vit D supplementation of 250–1000 IU/day) aligns with the standard of care supported by multiple pediatric societies [7,13,14]. Moreover, we are well-informed about the potential adverse effects associated with this intervention.

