**Assessment**					
	**First 48 h** **of Life**	**First 48 h** **of Life**	**4 Weeks of Age**	**8 Weeks of Age ***	**35 ± 2 Weeks** **of PCA**
Blood sample for 25(OH)D		X	X	X	X
Blood sample for PTH		X	X	X	X
Blood sample for IL-6		X	**	**	X
Sample collection for Ca/P metabolism			X	X	X
Renal ultrasound					X
Bone mass assessment					X
Adverse events		X ***	X ***	X ***	X ***

25(OH)D: 25-hydroxyvitamin D; PCA: postconceptional age; IL-6: interleukin 6; Ca/P: calcium/phosphorus; IL-6: interleukin-6. * Eight weeks postconceptional age, only for infants born before 26 weeks of gestation. ** Blood sample for IL-6 will be obtained; for a suspected case of late-onset sepsis, a bacteriological blood test will be conducted simultaneously, using a blood sample of at least 1 mL. *** Adverse events monitored from enrollment until hospital discharge.

**Table 2 nutrients-16-00700-t002:** Dosage change, depending on 25(OH)D serum concentration, based on Polish guidelines.

Rules of Vitamin D Supplementation						
Serum concentration of 25(OH)D	<20 ng/mL	20–30 ng/mL	30–50 ng/mL	50–75 ng/mL	>75 ng/mL	>100 ng/mL
Management	Increase supply by 100%	Increase supply by 50%	Maintain the current supply	Reduce the dose by 50%	No supplementation for 1–2 months, and then 50% of the previous dose	Stop supplementation, Assess calcemia and calcuria, consider resuming supplementation after reaching 25(OH)D concentration < 50 ng/mL with normocalcemia and normocalcuria

25(OH)D: 25-hydroxyvitamin D.

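### Section 2.11 justifies having no monitoring committee with a 250–1000 IU/day range that covers only the starting doses; as a smaller point, Table 2 raises the dose without looking at the same-visit calcium

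*Protocol article*

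**What the plan says.** **Dosing.** Section 2.6 starts the monitored arm at 1000 IU/day. The control arm gets 250 IU/day (extremely low birth weight) or 500 IU/day (above 1000 g), without later change. In the monitored arm, "vit D doses will be adjusted accordingly based on the 25(OH)D levels", using the national scheme reproduced in Table 2. Below 20 ng/mL the entry is "Increase supply by 100" per cent; at 20–30 ng/mL it is "Increase supply by 50" per cent. Calcium appears in Table 2 only in the column above 100 ng/mL, where supplementation stops.

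**Calcium.** Table 1 lists "Sample collection for Ca/P metabolism" at 4 weeks, at 8 weeks ("only for infants born before 26 weeks of gestation") and at close-out. Section 2.9.1 includes serum and urine calcium in these tests. It adds: "Hypercalcemia will be defined as a serum level of ≥2.75 mmol/L". It also says that "monitoring of both the 25(OH)D level and serum and urine calcium levels is recommended in this group of premature neonates".

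**Oversight.** Section 2.11 explains the absence of a data monitoring committee by saying of the intervention: "vit D supplementation of 250–1000 IU/day) aligns with the standard of care supported by multiple pediatric societies", with three guideline sources cited. It adds a second reason, that the possible adverse effects are well known.

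**The concern.** A statement of why a trial needs no independent safety oversight should describe the treatment that infants can actually receive. Section 2.11 describes a range whose top is the monitored arm's starting dose, yet the feature that sets this arm apart is that the dose can rise from there. The Introduction's account of the cited guidelines makes 1000 IU/day a meaningful boundary, so it matters on which side of it the intervention lies. An ethics committee reading section 2.11 alone would be judging a lower exposure than the scheme permits.

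The calcium point is separate and smaller. The protocol defines hypercalcaemia and collects the result at the visit where the dose is decided, but the increase rule does not use it. As printed, an infant with serum calcium of 2.75 mmol/L or more and 25(OH)D of 25 ng/mL would have the dose raised by 50%.

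**Working it through.** **1. Reproducing the stated range.** Starting doses in section 2.6 are 250, 500 and 1000 IU/day. Their minimum and maximum are 250 and 1000, so the range in section 2.11 is recovered from starting doses alone.

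**2. Applying Table 2 in the monitored arm.** New dose = current dose × factor.
- 20–30 ng/mL: 1000 × 1.5 = 1500 IU/day.
- Below 20 ng/mL: 1000 × 2 = 2000 IU/day.

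The stated upper limit is exceeded by a factor of 1.5 or 2 at the first increase.

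**3. Does the wording of Table 2 rescue the range?** Table 2 speaks of supply, and section 2.6 counts dietary intake from the second month. Section 2.6 gives 150–300 IU/kg from enteral feeds. For an assumed weight of 1 kg, total intake in IU/day is:

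| Reading | +50% | +100% |
|---|---|---|
| Supplement scaled, feeds added | 1500 + (150 to 300) = 1650–1800 | 2000 + (150 to 300) = 2150–2300 |
| Target already includes feeds | 1500 | 2000 |
| Supplement plus feeds scaled | 1.5 × (1150 to 1300) = 1725–1950 | 2 × (1150 to 1300) = 2300–2600 |

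All totals exceed 1000. Under the second reading the supplement alone would be 1500 − (150 to 300) = 1200–1350 IU/day, or 2000 − (150 to 300) = 1700–1850 IU/day. Only after the +50% step, with the richest feeds and a weight above about 500/300 = 1.67 kg, would the supplement alone fall below 1000, and the total would still be 1500.

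**4. The cited sources, as the Introduction reports them.** The American guideline suggests 200–400 IU/day. The European one gives 400–700 IU/kg/day with a ceiling of 1000 IU/day. The Polish one gives 800 IU/day in the first month and advises caution once the total passes 1000 IU, particularly below 1000 g birth weight. The Polish guideline is also the source of Table 2.

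**5. How many infants, and for how long.** The documents give no forecast for infants on 1000 IU/day. As an illustration, take the department's previous 45% below 30 ng/mL on 500 IU (Introduction; section 2.12) and subtract the 25 points that the trial is sized to detect: 0.20 × 54 = 10.8, about 11 infants. The 25% is in points because 80% versus 55% reproduces 54 per group (two-sided 0.05, power 80%), whereas a relative reduction, 80% versus 60%, would need 82.

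Time left between day 28 and 35 weeks is 35 − (GA + 4) = 31 − GA weeks: 7 at 24+0, 3 at 28+0, 1 at 30+0 and none from 31+0. So the count of 11 includes infants with no in-trial time at a raised dose. The most immature infants have the longest exposure.

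**6. Calcium with a low 25(OH)D.** The documents give no rate. If 1–5% of about 11 escalated infants were hypercalcaemic (assumption), that is 11 × 0.01 = 0.1 to 11 × 0.05 = 0.6 infants.

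**The case against.** **The scheme is national guidance and is openly disclosed.** The abstract, section 2.6 and Table 2 all show that doses can change, and the Polish source cited in section 2.11 also supplies Table 2. This stands in part: it gives raised doses some standard-of-care support. It does not make 250–1000 IU/day a correct description, and the same source carries the caution above 1000 IU.

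**Section 2.11 has a second reason.** Known adverse effects are a separate argument that does not depend on the range. This stands, and it is why the point concerns the statement and not the decision.

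**An article omits operational detail.** A calcium hold could sit in the full protocol. The Discussion says that calcium is measured to assess toxicity and prevent nephrocalcinosis, section 2.10 provides monthly meetings, and unblinded intensive-care staff may well hold a dose. This stands far enough to make the calcium point an improvement to a stated rule, not an error. It does not touch section 2.11, where a figure is printed and is too low. The absence of a stated maximum dose is likewise detail that an article may leave out, and is not pressed.

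**Stronger readings to avoid.** A reader might multiply the planned 55% by 54 and say that about 30 monitored infants will be escalated. The 55% comes from the sample-size assumption and fits poorly with 45% on half the dose in the same department. A reader might also compound two doublings to 4000 IU/day; that needs birth before 26 weeks and a level below 20 ng/mL at both 4 and 8 weeks.

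**Conclusion.** **Section 2.11 is wrong as written.** It gives the range of starting doses as the range of the intervention and rests part of its oversight rationale on it. The first Table 2 increase takes a monitored infant on 1000 IU/day to about 1500 or 2000 IU/day, and total intake exceeds 1000 IU/day on each reading tested. This follows from the printed text; only the exact totals depend on the assumed 1 kg weight.

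**The missing calcium check is a cheap improvement.** The printed rule can direct an increase that a result due at the same visit would argue against. The likely number of infants is very small, on an assumed rate that the documents do not supply.

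A reader might infer that the trial needs a monitoring committee or that the escalation scheme is unsafe. The documents support neither: the scheme has a national source, supplementation stops above 100 ng/mL, and the second reason in section 2.11 remains. The primary endpoint is also unaffected, because the day-28 sample is taken before any Table 2 adjustment. The point should be fixed, at modest weight.

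**What to change.** **Section 2.11 (correction).** Replace the range with one that includes Table 2: starting doses of 250–1000 IU/day, rising in the monitored arm to about 1500 or 2000 IU/day at the first increase and adjusted again at later samples. Then restate on that range why no committee is needed, addressing the 1000 IU/day cap and caution reported in the Introduction. The known adverse effects and the national source of the scheme may still carry the argument.

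**Section 2.6 and Table 2 (improvement).** Add one sentence: serum and urine calcium from the same visit are reviewed before any increase, and no increase is made while hypercalcaemia (2.75 mmol/L or more) or hypercalciuria is present, pending clinical review.

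**Cost.** Both changes are wording only; no new test or visit is needed. The calcium sentence brings a short wait for the result and slightly fewer increases in the monitored arm.

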### 2.7. Primary Outcome

The percentage of infants with deficient or suboptimal 25(OH)D levels at 28 ± 2 days of age will be the primary endpoint. The 25(OH)D levels will additionally be measured at 35 ± 1 weeks of PCA. Neonatal staff will obtain venous samples of 0.3 mL to assess the 25(OH)D serum concentration. The study site will utilize the VIDAS automated quantitative test (bioMérieux, Marcy l’Etoile, France) to measure 25(OH)D concentrations. In Poland, the diagnostic thresholds for serum 25(OH)D concentrations are as follows [7]: <20 ng/mL (50 nmol/L) indicates vitamin D deficiency;
>20 ng/mL (50 nmol/L) and <30 ng/mL (75 nmol/L);≥30 ng/mL (75 nmol/L) up to 50 ng/mL (125 nmol/L) reflect adequate to optimal vitamin D status;>50 ng/mL (125 nmol/L) up to 100 ng/mL (250 nmol/L) indicate a high vitamin D supply;>100 ng/mL (250 nmol/L) reflect an increased risk for intoxication [7].

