## Abstract

Vitamin D deficiency can escalate prematurity bone disease in preterm infants and negatively influence their immature immunology system. Infants born at 24 + 0/7 weeks to 32 + 6/7 weeks of gestation will be considered for inclusion. Cord or vein blood samples will be obtained within 48 h after birth for 25-hydroxyvitamin D level measurements. Parathyroid hormone and interleukin-6 levels will be measured. Infants will be randomized to the monitored group (i.e., an initial dose of 1000 IU/day and possible modification) or the controlled group (i.e., 250 IU/day or 500 IU/day dose, depending on weight). Supplementation will be monitored up to a postconceptional age of 35 weeks. The primary endpoint is the percentage of infants with deficient or suboptimal 25-hydroxyvitamin D levels at 28 ± 2 days of age. 25-Hydroxyvitamin D levels will be measured at postconceptional age 35 ± 2 weeks. Secondary goals encompass assessing the occurrence of sepsis, osteopenia, hyperparathyroidism, and interleukin-6 concentration. The aim of this study is to evaluate the efficacy of monitored vitamin D supplementation in a group of preterm infants and ascertain if a high initial dosage of monitored vitamin D supplementation can decrease the occurrence of neonatal sepsis and metabolic bone disease.

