### 2.2. Setting and Participants

All infants admitted to the Department of Neonatology and Intensive Care at the Medical University of Warsaw (Warsaw, Poland) and born at 24 + 0/7 weeks to 32 + 6/7 weeks of gestation will be considered for inclusion. Our tertiary perinatal center has an annual number of births of approximately 2500 infants, including an average of 80 infants aged <33 weeks of gestation. 25(OHD) neonatal birth concentration strongly correlates with pregnant vit D supplementation. According to the Polish Society of Gynecologists and Obstetricians, it is recommended to supplement vit D at a dose of 1500–2000 IU/day during pregnancy [19]. However, the available multivitamin supplements for pregnant women in Poland vary from 400 IU to 2000 IU. The parents of the infants will provide informed consent. Patients will be randomly assigned to the monitored group or the controlled group. We will collect a cord or vein blood sample within the first 48 h of life to evaluate 25(OH)D levels at birth. Blood samples will be taken simultaneously with other laboratory tests so as not to expose the newborn to additional blood donations. Additionally, the maternal 25(OH)D level and the neonatal birth levels of PTH and IL-6 will be measured. Once infants reach a daily enteral feeding volume of 30 mL/kg, they will receive an initial vitamin D dose. We will continue to monitor the supplementation until 35 weeks of PCA.

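### No level-based dose adjustment can precede the day-28 primary endpoint, so it compares two initial dosing regimens and cannot show the efficacy of monitored supplementation

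*Protocol article*

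**What the plan says.** The abstract gives the aim: "The aim of this study is to evaluate the efficacy of monitored vitamin D supplementation in a group of preterm infants". The end of the Introduction and the Discussion repeat it as effectiveness of monitored supplementation.

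Section 2.6 fixes the starting doses. For one arm, "Infants in the monitored group will receive an initial dose of 1000 IU of vit D"; for the other, "infants in the controlled group will receive 250 IU for extremely low birth weight infants and 500 IU for infants weighing above 1000 g". Neither depends on the 25(OH)D level at birth. The same section places the first on-treatment sample at 28 ± 2 days and then says: "In the monitored group, vit D doses will be adjusted accordingly based on the 25(OH)D levels".

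Section 2.7 uses that same sample for the primary outcome: "The percentage of infants with deficient or suboptimal 25(OH)D levels at 28 ± 2 days of age will be the primary endpoint". It treats the later measurement as an extra: "The 25(OH)D levels will additionally be measured at 35 ± 1 weeks of PCA". The abstract gives that later visit a different tolerance: "25-Hydroxyvitamin D levels will be measured at postconceptional age 35 ± 2 weeks". Section 2.2 sets the end of follow-up for dosing: "We will continue to monitor the supplementation until 35 weeks of PCA".

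**The concern.** The arm is named for monitoring and the aim is about monitoring, but the primary endpoint is read before monitoring can change any dose. A positive result would show that a higher starting dose leaves fewer infants with low 25(OH)D at four weeks. Reported under the stated aim, it would be taken as evidence that measuring levels and adjusting doses works, which the comparison does not test.

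The natural place to look for an effect of adjustment is the 35-week visit. For infants born late in the eligible range, that visit falls close to day 28 or before it, so pooling all infants at 35 weeks mixes those who could have had an adjusted dose with those who could not.

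**Working it through.** **The plan's own figure.** Section 2.12 uses 80% against 55% (a decrease of 25 points), α = 0.05 and power 80%. Taking α as two-sided, with pooled proportion 0.675:

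n = [1.960·√(2·0.675·0.325) + 0.842·√(0.80·0.20 + 0.55·0.45)]² / 0.25² = 53.9, so 54 per group.

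This matches the stated 54. The number needed does not change because of this point. Whether 80% is the right control rate is a separate question.

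**Order of events up to the primary sample.**
- Birth sample: section 2.2 takes it to describe the level at birth. No section links it to a dose.
- Initial dose: fixed by arm, and in the control arm by weight (section 2.6).
- First on-treatment 25(OH)D: 28 ± 2 days (section 2.6, Table 1). The Introduction says the guideline behind the adjustment scheme advises a first assessment after 4 weeks of supplementation.
- Adjustment by Table 2: monitored arm only, described after the day-28 sample.
- Stop above 100 ng/mL: applies to both arms (section 2.6), so it is not the monitored titration.

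So the number of infants with a level-adjusted dose at the primary sample is zero, and the arms differ up to then by initial regimen only.

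**Time left for an adjusted dose before 35 weeks.** Age in days at 35+0 = 245 − gestational age at birth in days, counting birth as day 0.

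| Birth | Days | Age at 35+0 | Days from day 28 to 35+0 |
|---|---|---|---|
| 24+0 | 168 | 77 | +49 |
| 28+6 | 202 | 43 | +15 |
| 29+0 | 203 | 42 | +14 |
| 31+0 | 217 | 28 | 0 |
| 31+1 | 218 | 27 | −1 |
| 32+6 | 230 | 15 | −13 |

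In the 24–28 week stratum there are 15 to 49 days between day 28 and 35+0. In the 29–32 week stratum the interval runs from 14 days after day 28 to 13 days before it. If 35 weeks is read as completed weeks, to 35+6 (251 days), births at 31+1 to 31+6 reach the end on days 33 to 28, and births at 32+0 (224 days) on day 27. The boundary moves by less than a week.

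**Order of the two visits.** The tolerance is ± 1 week in sections 2.6, 2.7, 2.8.2, 2.8.3, 2.8.4 and 2.9.1, and ± 2 weeks in the abstract and Table 1.

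- Opening: ± 1 week opens at 34+0 (238 days), which is day 28 for birth at 30+0 (238 − 210). ± 2 weeks opens at 33+0 (231 days), which is day 28 for birth at 29+0 (231 − 203). Infants born later than these can have the 35-week sample before day 28.
- Closing, compared with the earliest primary sample on day 26:

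| Reading of the window | Closes at | Born 32+3 (227 d) | Born 32+6 (230 d) |
|---|---|---|---|
| ± 1 week, exact | 36+0 (252 d) | day 25 | day 22 |
| ± 1 week, completed weeks | 36+6 (258 d) | day 31 | day 28 |
| ± 2 weeks, exact | 37+0 (259 d) | day 32 | day 29 |

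Only the first reading puts the whole 35-week window before day 26. The unresolved tolerance therefore decides which visit comes first for these infants.

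**The case against.** The strongest reply is that the arm is openly a package. The abstract describes it as a starting dose with possible modification, and the second half of its aim refers to a high initial dose in connection with sepsis and bone disease. There is also a reason to test the starting dose. The Introduction reports that about 45% of infants in the department's earlier study were deficient or suboptimal at 4 weeks on 500 IU, and that both arms of that study began on the same dose. This stands: a comparison of starting regimens at day 28 is a legitimate question. It does not rescue the claim about monitoring, because the modification part of the package has not yet happened at day 28.

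A reader might infer that the primary comparison is biased or its sample size wrong. The documents do not support that: the comparison is randomised, and the sample size is built on the same endpoint.

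A reader might also infer that oversupply goes unexamined because the primary endpoint counts only low levels. It cannot count in the primary endpoint, but the high and toxic bands are defined in section 2.7. Hypercalcaemia, hypercalciuria and nephrocalcinosis are assessed in section 2.9.1, and intoxication is covered in section 2.9.2.

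**Conclusion.** The point holds as a mismatch between aim and endpoint. As written, the primary result can support a conclusion about initial dosing regimens at 28 days and none about monitoring. This rests on the stated order of sampling and adjustment, and on the absence of any text tying the birth level to a dose.

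Infants born from about 31 weeks have little or no time on an adjusted dose before 35 weeks. The exact boundary depends on whether 35 weeks means 35+0 or 35+6.

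Two stronger readings should not be drawn. First, that the 35-week window closes before the earliest primary sample for births at 32+3 to 32+6: this is true only if ± 1 week ends at 36+0, and fails under ± 2 weeks or completed weeks. Second, that the 35-week result in the 24–28 week stratum would isolate monitoring. The arms still differ in starting dose, so that result reflects initial dose plus adjustment together. The same applies to the 8-week sample, which Table 1 restricts to infants born before 26 weeks. No endpoint in this design separates the two.

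**What to change.** 1. State the primary objective, and the conclusion to be drawn from it, as a comparison of the two initial dosing regimens on 25(OH)D status at 28 days.
2. Use 25(OH)D status at the 35-week visit as a secondary readout of the whole strategy (initial dose plus adjustment). Include the proportion within 30–50 ng/mL, the adequate-to-optimal band of section 2.7, so that low and high levels both count. Report it separately for the 24–28 and 29–32 week strata, and state that no endpoint isolates monitoring because the arms start on different doses.
3. Reconcile the 35-week window to one value throughout, say whether it is counted in exact or completed weeks, and state which sample serves which endpoint when the day-28 and 35-week visits coincide or reverse.

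These are changes of wording, endpoint hierarchy and reporting. The 25(OH)D samples are already scheduled, and neither the doses nor the sample size changes. The cost is a narrower primary claim. The documents give no stratum sizes and no power within strata, so the stratified 35-week results should be presented as estimates with confidence intervals.
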